#### Analysis: effectiveness evaluation

Descriptive statistics will be used to summarize outcome values at baseline, 6 months and 12 months. Means and standard deviations will be used for continuous outcomes, and frequency and percentages will be used for categorical outcomes. Intention-to-treat analyses using analysis of covariance (ANCOVA) will be used to assess group differences in continuous outcomes from baseline to T2 in order to determine if the intervention was effective over the intervention period. The outcomes include: PRQ-2000, CESD-10, GAD-7, VR-12 PCS, VR-12 MCS, the PPC, CCCQ, and the IC-PREMs. The ANCOVA model will use the 6-month outcome value as the dependent variable, the group indicator as the independent variable and the baseline outcome value as the covariate. Model results will be expressed as mean group differences with accompanying 95% confidence limits. Quantile regression will also be used to examine the treatment effect over a broader range of values (beyond the mean) for the outcome variables. Assessment of group differences in continuous outcomes from T_2_ to T_3_ will be assessed using ANCOVA and will be aimed at assessing the sustainability of the intervention effects (see Table 1).

Z tests of proportions and McNemar tests will be used to assess changes within each group in the number of participants with acute care episodes and the number of acute care episodes from baseline to T_2_, and from T_2_ to T_3_ Acute care episodes include emergency department visits and hospital admissions. Risk difference (intervention risk – control risk) and accompanying 95% confidence limits will be calculated for 6 months for emergency department visits and hospital readmissions for 6 months. As was noted earlier, acute care episodes will be identified using administrative data from IC/ES, and self-reported data from the HSSUI. Due to the highly skewed nature of cost data, a non-parametric test will be used to compare the change in health and social service use and costs from baseline to T_2_ and from T_2_ to T_3_ for the two groups. Outliers are particularly common for certain healthcare costs such as hospital admissions, thus we will conduct a sensitivity analysis to assess the impact of outliers on the cost comparison.

Subgroup analyses will be conducted for the VR-12 outcomes to determine if the intervention is effective for subgroups of patients from baseline to T2. The following baseline variables have been selected a priori for testing subgroup effects: age, sex, number of chronic conditions, depressive symptoms (CESD-10), site, and dose of the intervention (number of home visits and telephone contacts). Multiple imputation will be used to address missing data. All data analyses will assume a level of significance of 0.05 and be performed using SAS Version 9.4.

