**Methods:**

Participants will be considered eligible if they are > 65 years, planned for discharged from hospital to the community in three Ontario locations, self-report at least two chronic conditions, and screen positive for depressive symptoms. A total of 216 eligible and consenting participants will be randomly assigned to the control (usual care) or intervention (CAST) arm. The intervention consists of tailored care delivery comprising in-home visits, telephone follow-up and system navigation support. The primary measure of effectiveness is mental health functioning of the older adult participant. Secondary outcomes include changes in physical functioning, depressive symptoms, anxiety, perceived social support, patient experience, and health and social service use and cost, from baseline to 6- and 12-months. Caregivers will be assessed for caregiver strain, depressive symptoms, anxiety, health-related quality of life, and health and social service use and costs. Descriptive and qualitative data from older adult and caregiver participants, and the nurse interventionists will be used to examine implementation of the intervention, how the intervention is adapted within each study region, and its potential for sustainability and scalability to other jurisdictions.

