#### Effectiveness measures and data sources

The effectiveness of the CAST intervention on older adults and their caregivers will be evaluated using a range of patient and caregiver-relevant measures. A summary of these measures, including their description, related variables/outcomes, and time point(s) collected, and methods of analysis, are summarized in Table 1.

**Table 1 Tab1:** CAST Study Outcome Measures Summary

Outcome	Measure	Group*	Timepoint	Method of Analysis
Mental functioning	Mental Component Score of VR-12 (MCS) [51, 55]	PT, CG	T_1_, T_2_, and T_3_	-Descriptive analyses -T1-T2 (Treatment Effect): ANCOVA, complete case and multiple imputation analyses, subgroup analyses, quantile regression -T2-T3 (Sustainability): ANCOVA, complete case and multiple imputation analyses, subgroup analyses
Physical functioning	Physical Component Score (PCS) of VR-12 [51, 55]	PT, CG	T_1_, T_2_, and T_3_	-Descriptive analyses -T1-T2 (Treatment Effect): ANCOVA, complete case and multiple imputation analyses, subgroup analyses, quantile regression -T2-T3 (Sustainability): ANCOVA, complete case and multiple imputation analyses, subgroup analyses
Depressive symptoms	CESD-10 [56]	PT, CG	T_1_, T_2_, and T_3_	-Descriptive analyses -T1-T2 (Treatment Effect): ANCOVA, complete case and multiple imputation analyses, quantile regression -T2-T3 (Sustainability): ANCOVA, complete case and multiple imputation analyses
Anxiety symptoms	Generalized Anxiety Disorder scale (GAD-7) [57]	PT, CG	T_1_, T_2_, and T_3_	-Descriptive analyses -T1-T2 (Treatment Effect): ANCOVA, complete case and multiple imputation analyses, quantile regression -T2-T3 (Sustainability): ANCOVA, complete case and multiple imputation analyses
Perceived social support	Personal Resource Questionnaire (PRQ-2000) [58]	PT	T_1_, T_2_, and T_3_	-Descriptive analyses -T1-T2 (Treatment Effect): ANCOVA, complete case and multiple imputation analyses, quantile regression -T2-T3 (Sustainability): ANCOVA, complete case and multiple imputation analyses
Communication between patients and providers	Patient-Provider Communication questionnaire [59]	PT, CG	T_1_ and T_2_	-Descriptive analyses -T1: z test of proportions for group comparison, complete case analysis -T2: z test of proportions for group comparison, complete case analysis

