Fourth, objective, reliable and valid measures will be used to assess a variety of patient-relevant outcomes, addressing a gap in the current literature that focuses predominantly on hospital readmissions as an outcome. Fifth, the study will evaluate the sustainability of the intervention effects by measuring the effectiveness of the intervention 6-months following completion of the intervention. Sixth, intervention fidelity will be enhanced by multiple approaches. Notably, the CTCs will be provided training, a standardized training manual, and regular meetings held with the research team throughout the intervention period to enhance the fidelity of intervention implementation. Lastly, the intervention will be evaluated in multiple sites and in diverse communities, which will enhance the generalizability of the results to other settings, as it reflects the diversity of the target population.

Conversely, there are some limitations to the study that warrant acknowledgement. First, sampling bias may influence the results, as those who volunteer to participate may be more likely to be receptive to the intervention. We will assess the extent of non-response bias by comparing the characteristics of study participants to those who decline participation in the study on their characteristics at baseline. Second, the use of a proxy respondent as a source of data for the study participants with limitations in cognition, physical health or language, may result in either an overestimation or an underestimation of the results.

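### The only inferential 12-month analysis of the continuous outcomes is a T2-to-T3 ANCOVA, which does not estimate the between-group effect at 12 months that the protocol promises

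*Protocol article*

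**What the plan says.** Under Analysis: effectiveness evaluation, the protocol writes out one ANCOVA, for the treatment period: "The ANCOVA model will use the 6-month outcome value as the dependent variable, the group indicator as the independent variable and the baseline outcome value", the last of these serving to adjust for the starting level. For the follow-up period it names only a method and an interval: comparisons of the arms over T2-T3 "will be assessed using ANCOVA and will be aimed at assessing the sustainability of the intervention effects". No dependent variable or covariate is given for that second model.

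Table 1 repeats the interval. For the mental component score (MCS) the 12-month entry reads "T2-T3 (Sustainability): ANCOVA, complete case and multiple imputation analyses, subgroup analyses". A T2-T3 ANCOVA is also listed for the physical component score, CESD-10, GAD-7, PRQ-2000 and caregiver strain. Neither the text nor Table 1 states a T1-T3 comparison. Beyond the T2-T3 ANCOVA, the continuous outcomes at 12 months get descriptive summaries only.

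Two other places describe a different target. The Abstract defines the secondary outcomes as changes "from baseline to 6- and 12-months". The Discussion lists as a strength that "the study will evaluate the sustainability of the intervention effects by measuring the effectiveness of the intervention 6-months following completion of the intervention".

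For service use and costs, the cost section and the analysis section both speak of comparing arms on change from T2 to T3. Table 1 gives a Mann-Whitney U test for that interval.

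**The concern.** Whether the benefit lasts to 12 months is a randomised question: how far apart are the arms at T3, given where they started? A model confined to the T2-T3 interval answers something else. T2 falls at the end of the six-month intervention, so the T2 value is a post-randomisation outcome. Patients in the two arms with the same T2 score are no longer a randomised comparison, and adjusting for that score removes part of any effect already achieved.

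Two misreadings could follow. A fully sustained benefit could be reported as no significant sustainability effect. A benefit that faded, with no harm at 12 months, could be reported as a significant difference in favour of usual care.

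**Working it through.** **Inputs.** From Sample size: MCS difference 6.5, SD 15.0, power 80%, alpha 0.05 (taken as two-sided), attrition 20%, total 216. From Randomization and blinding: 1:1 allocation. Assumed, because the protocol gives no value: within-arm correlation ρ between visits, the same for every pair, over 0.4 to 0.7; equal SDs; 20% loss by 12 months.

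**Reproducing the plan's figure.** n per arm = 2·(1.96 + 0.842)²·15²/6.5² = 83.6, so 84. Then 84/0.8 = 105 per arm, 210 in total. The t-based version gives 85 per arm, 107 after attrition, 214 in total, and 216 when rounded up to three equal sites. The stated 216 is reproduced. Completers: 216 × 0.8 / 2 = 86 per arm.

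**What each model estimates.** Let d2 and d3 be the true group differences at T2 and T3.
- T3 on group and T2: d3 − ρ·d2
- T3-minus-T2 change on group and T1: d3 − d2
- T3 on group and T1: d3

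The first is zero when d3 = ρ·d2, so a null result marks neither a sustained nor a lost effect. The second is zero when the effect is fully sustained, and also when there was never any effect.

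**Standard error.** SE = 15·√(1 − ρ²)·√(2/86 + D/(170·225)), where D is the expected squared arm difference in the covariate. For T1, D = 2·225/86 = 5.23, so the last root is 0.1530. For T2, D = 6.5² + 5.23 = 47.48, and the root is 0.1565. The chance of significance is Φ(|coefficient|/SE − 1.974).

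Example at ρ = 0.6, T2-adjusted: SE = 15 × 0.8 × 0.1565 = 1.88.
- Fully sustained: 6.5 − 0.6 × 6.5 = 2.60; 2.60/1.88 = 1.38; power Φ(−0.59) = 28%.
- Fully faded: 0 − 3.90 = −3.90; 3.90/1.88 = 2.08; chance of significance against CAST Φ(0.10) = 54%.

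| ρ | Sustained (d3 = 6.5): T2-adjusted coefficient | Power, T2-adjusted | Power, T1-adjusted | Faded (d3 = 0): T2-adjusted coefficient | Significant against CAST, T2-adjusted |
|---|---|---|---|---|---|
| 0.4 | +3.90 | 44% | 87% | −2.60 | 22% |
| 0.5 | +3.25 | 35% | 90% | −3.25 | 35% |
| 0.6 | +2.60 | 28% | 94% | −3.90 | 54% |
| 0.7 | +1.95 | 21% | 98% | −4.55 | 77% |

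With T1 adjustment, a fully faded effect is significant against CAST in about 2.5% of trials. With half the effect retained (d3 = 3.25), the T2-adjusted coefficient is +0.65, 0, −0.65 and −1.30 across the four values of ρ. Simulation with equal correlations (40,000 trials per scenario) agrees with the table within one percentage point.

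**Change-score reading.** SE = 15·√(2(1 − ρ))·0.1530, which is 2.51 at ρ = 0.4 and 1.78 at 0.7. A faded effect has coefficient −6.5 and is significant against CAST in 73% to 95% of trials.

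**Smaller 6-month effect.** With d2 = 3.25 and d3 = 0, the T2-adjusted coefficient is −1.30 to −2.28. D becomes 15.79, the root 0.1538, and the chance of significance against CAST 9% to 28%.

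**Service use and costs.** If one arm costs k less in both months 0-6 and months 6-12, the difference in change is (−k) − (−k) = 0. A steady saving disappears from a comparison of change.

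**The case against.** The strongest reply is that the faulty model is inferred. The protocol never writes T2 as the covariate, the document is a condensed article, and the Abstract and Discussion fit a T3 comparison adjusted for baseline. That stands as a caution: a reader might conclude that the protocol specifies the 6-month value as covariate, and it does not. The interval T2-T3 is stated twice, however, and neither natural reading of it (T2 as covariate, or T2-T3 change) estimates the 12-month effect.

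Other stronger inferences also go too far.
- That the analysis removes the whole 6-month effect: T2 adjustment removes only the share ρ.
- That it says nothing about sustainability: read beside the T1-T2 estimate and the descriptive T3 means it carries some information, although no planned test or interval estimates d3.
- That the sign generally reverses: this needs ρ > d3/d2. With half the effect retained, the coefficient is still positive below ρ = 0.5.
- That one false-harm percentage can be quoted: widening ρ to 0.3 to 0.8 moves it from about 14% to 96% by the same formula, and a smaller 6-month effect lowers it.

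The power contrast does not depend on a favourable T1-T3 correlation. With no correlation at all, a plain T3 comparison with 86 per arm has 81% power for 6.5 points.

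On costs, the Mann-Whitney entry in Table 1 could mean a comparison of 6-12 month totals, which would be sound. The text says change, so this part is a conditional point and not an established error.

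**Conclusion.** The concern holds in this form: for the continuous outcomes, the stated 12-month analysis covers the wrong interval for the stated aim, and the Analysis section and Table 1 do not match the Abstract and Discussion. If T2 is the covariate, power for a fully sustained effect is about 44% down to 21% instead of 87% to 98%. A fully faded effect looks significantly harmful in about 22% to 77% of trials instead of about 2.5%. These figures rest on SD 15, a 6-month effect of 6.5, 86 completers per arm, and an assumed ρ of 0.4 to 0.7.

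A reader might infer that the trial's main result is at risk. The documents do not support that: the primary T1-T2 analysis uses the baseline covariate and is untouched. The weakness is confined to the sustainability claim and, if change is meant literally, to the T2-T3 cost comparison.

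**What to change.** In the Analysis section and in Table 1, define the sustainability analysis as the between-group difference at T3 adjusted for the T1 value of the same outcome, reported with its 95% CI. A repeated-measures model with T2 and T3 as responses and baseline as covariate, reporting the group difference at each visit, would serve equally well. Keep any T2-T3 contrast as descriptive. This brings both places into line with the Abstract and Discussion.

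For service use and costs, also compare the arms on 6-12 month totals and on cumulative 0-12 month totals.

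The cost is a few sentences and some code. T1, T2 and T3 are already scheduled, so no further data or patients are needed.

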### Research questions

The study addresses three research questions:
What is the effect of a new, nurse-led hospital-to-home transitional care intervention compared to usual care on health outcomes and costs for older adults with MCC and depressive symptoms and their caregivers?How is the new care transition intervention adapted and implemented in diverse settings?What is required to sustain and scale up the intervention?

It is hypothesized that, compared to usual care, the intervention will result in improvements in health outcomes for older adults with MCC and depressive symptoms while reducing the utilization of expensive healthcare services (e.g., hospitalization).

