Client-centredness of care	Adapted Client-Centred Care Questionnaire (CCCQ) [60]	PT, CG	T_1_, T_2_, and T_3_	-Descriptive analyses -T1: z test of proportions for group comparison, complete case analysis -T2: z test of proportions for group comparison, complete case analysis
Care experience	Integrated Care Patient-Reported Experience Measures (IC-PREMs) [61]	PT, CG	T_1_, and T_2_	-Descriptive analyses -T1: z test of proportions for group comparison, complete case analysis -T2: z test of proportions for group comparison, complete case analysis
Unmet care needs	Unmet Care Needs questionnaire	PT, CG	T_1_, T_2_, and T_3_	-Descriptive analyses - T1: z test of proportions for group comparison, complete case analysis -T2: z test of proportions for group comparison, complete case analysis
Caregiver strain	Modified Caregiver Strain Index (CSI) [62]	CG	T_1_, T_2_, and T_3_	-Descriptive analyses -T1-T2 (Treatment Effect): ANCOVA, complete case analysis -T2-T3 (Sustainability): ANCOVA, complete case analysis
Utilization of health and social services and associated costs	Institute for Clinical Evaluative Sciences (IC/ES), Health and Social Services Utilization Inventory (HSSUI) [63, 64]	PT, CG	T_1_, T_2_, and T_3_	-Descriptive analyses -T1-T2 (Treatment Effect): Mann-Whitney U test, complete case analysis, Hazard Ratio (95% CI) & Risk Difference (95% CI) for 30, 90 &180-day ED visits and hospital admissions -T2-T3 (Sustainability): Mann-Whitney U test, complete case analysis

*PT = patient; CG = caregiver, *T1 = baseline; T2 = 6-month; T3 = 12 months

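### Acute care episodes are given within-group z and McNemar tests as effectiveness analyses; these do not compare CAST with usual care, do not fit a count, and do not match Table 1

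*Protocol article*

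**What the plan says.** The hypothesis under Research questions is comparative: "compared to usual care, the intervention will result in improvements in health outcomes", together with lower use of expensive services such as hospitalization.

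Under Analysis: effectiveness evaluation, the sentence on acute care reads "Z tests of proportions and McNemar tests will be used to assess changes within each group". It then names its endpoints ("in the number of participants with acute care episodes and the number of acute care episodes from baseline to"), with the first interval closing at T2 and a second one running on to T3. One sentence therefore applies the same two tests to a binary endpoint (any episode) and to a count (how many episodes).

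The same paragraph also plans two comparisons between arms:
- An estimate for both kinds of acute care event: "Risk difference (intervention risk – control risk) and accompanying 95% confidence limits will be calculated for 6 months".
- A two-arm test, chosen because costs are skewed: "a non-parametric test will be used to compare the change in health and social service use and costs from baseline to" (the first interval closes at T2, the second at T3).

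Table 1 (Effectiveness measures and data sources) lists Mann-Whitney U for utilization in both periods. Within T1 to T2 it adds "Hazard Ratio (95% CI) & Risk Difference (95% CI) for 30, 90 &180-day ED visits and hospital admissions". For the later period it has only "T2-T3 (Sustainability): Mann-Whitney U test, complete case analysis". It lists no z or McNemar test for utilization.

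**The concern.** A before-after test inside one arm measures time trend plus any treatment effect, and randomisation does not separate the two. Finding a significant fall under CAST and a non-significant one under usual care is not evidence that the arms differ.

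The design makes a trend likely. Eligibility criteria admits people as they are about to leave hospital, and Participant flow, assessments and timeline puts baseline within two weeks after discharge. Any look-back from baseline longer than two weeks reaches the index stay unless that stay is excluded, and the article neither states the look-back nor excludes the stay.

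At stake is a statement that CAST reduced hospital use, supported by a pre-planned test that could equally be significant under usual care.

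**Working it through.** **Inputs from the article.** Total 216, 1:1 allocation, 20% attrition, alpha 0.05. Completers per arm: 216 × 0.8 / 2 = 86.4, taken as 86. The article gives no acute care event rates, so all rates below are assumptions.

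**The plan's own figure.** The sample size concerns VR-12 MCS, not acute care. With difference 6.5, SD 15, 80% power and two-sided 0.05, n = 2 × (1.96 + 0.842)² × 15² / 6.5² gives 84 per arm. Then 84 / 0.8 = 105 per arm, or 210 in total. A t-based calculation gives 85 per arm, 107 after attrition, 214 in total. The stated 216 (3 × 72) is consistent with this and is not in dispute.

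**Within-arm tests with no treatment effect.** Simulation: 10,000 trials per row, 86 per arm, latent within-person correlation 0.3, the same fall in both arms, exact McNemar in each arm, and a two-proportion z test between arms at follow-up.

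| Share with an episode, baseline to follow-up (assumed) | Exactly one arm significant | Both arms significant | Between-arm test significant |
|---|---|---|---|
| 50% to 50% | 6.4% | 0.1% | 5.8% |
| 60% to 50% | 37.5% | 6.2% | 5.2% |
| 60% to 45% | 49.8% | 27.0% | 5.4% |
| 65% to 50% | 50.2% | 27.6% | 6.2% |
| 70% to 50% | 32.2% | 63.7% | 5.6% |
| 100% to 50% | 0% | 100% | 5.5% |
| 100% to 35% | 0% | 100% | 5.1% |

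If each arm is significant with probability p, exactly one is significant with probability 2p(1 − p), which cannot exceed 0.50. In the 70% to 50% row, p = 0.637 + 0.322 / 2 = 0.798, and 2 × 0.798 × 0.202 = 0.32, as simulated.

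The 100% rows show the case where the index stay counts at baseline. All discordant pairs then point downwards, and six are enough: 2 × 0.5⁶ = 0.031. So if only 6 of 86 people had no admission in the following window, that arm would already be significant.

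**Validity of each named test.** With 86 pairs, 50% at both times and no change, rejection rates were:

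| Latent correlation | z test treating the samples as independent | Exact McNemar |
|---|---|---|
| 0 | 5.4% | 3.5% |
| 0.3 | 3.4% | 3.4% |
| 0.6 | 1.3% | 3.0% |

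McNemar keeps its level. The z test uses the wrong variance and becomes conservative as the correlation rises. Neither analyses a count.

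**The planned between-arm risk difference.** The 95% half-width is 1.96 × √(2p(1 − p) / 86): 12.0 points at p = 0.20, 14.3 at 0.35 and 14.9 at 0.50.

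**Text against Table 1.**

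| Analysis | Text | Table 1 |
|---|---|---|
| Within-group z and McNemar | both periods | not listed for utilization |
| Risk difference between arms | 6 months | 30, 90 and 180 days |
| Hazard ratio | not listed | listed, T1 to T2 |
| Non-parametric two-group test | both periods | Mann-Whitney U, both periods |

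For T2 to T3, neither place has a between-arm risk estimate.

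**The case against.** The strongest reply is that the arms are already compared. A risk difference with a 95% confidence interval is inference on the randomised contrast. Mann-Whitney covers both periods and can handle counts, and Table 1 adds hazard ratios and further windows. This stands. A reader might infer from the z and McNemar sentence that the plan never compares CAST with usual care on acute care; the rest of the same paragraph and Table 1 show otherwise.

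A reader might also infer that both tests are invalid for paired data. McNemar is the standard test for a paired binary endpoint. Only an independent-samples z test has that fault, and it errs towards too few rejections.

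A third tempting reading is that a fall in both arms is certain. It depends on the look-back and on whether the index stay counts. The questionnaire with the utilization inventory is an additional file that is not shown. The argument concerns T1 to T2 only, and an equal fall in both arms does not bias the between-arm risk difference.

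The 50% figure also sits at the mathematical maximum for discordant arms, and the simulated rates matter only if readers rely on the within-group results over the planned between-arm interval. Some of the text-table gap is elaboration: 180 days matches 6 months. Finally, the time origin of the windows and adjustment for site are details an analysis plan can carry, so they are not part of this point.

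None of this gives the within-group tests a role in answering the stated question, makes either test suit a count, or removes the mismatch between text and table.

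**Conclusion.** The point holds in limited form. The within-group tests are listed under effectiveness but cannot answer the comparison with usual care, and neither fits the number of episodes. The z test, if run as for independent samples, also ignores the pairing.

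Under no treatment effect and the moderate equal falls assumed here, one arm alone is significant in roughly 30% to 50% of trials, against about 5% for a between-arm comparison. With no fall the figure is about 6%. If the index stay counts at baseline, both arms are significant in essentially every trial. These sizes rest on assumed event rates, 86 completers per arm and a latent correlation of 0.3.

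Valid between-arm analyses exist, but the text and Table 1 do not agree on them, and T2 to T3 has only the non-parametric one. Severity is should-fix: service use is a secondary outcome, and the primary VR-12 MCS analysis is a between-group ANCOVA.

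**What to change.** - Make between-arm estimates the effectiveness analysis of acute care episodes in both periods: a risk difference with 95% confidence interval for any episode, and a between-arm count method for the number of episodes (for example a negative binomial rate ratio, or the Mann-Whitney test already planned).
- Remove the within-group z and McNemar tests, or label the before-after figures descriptive.
- State the baseline look-back and exclude the index stay from any baseline count.
- Make the analysis text and Table 1 list the same measures, windows and tests, including a between-arm risk estimate for T2 to T3.

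The cost is wording and analysis code. No change to recruitment, sample size or data collection is needed.

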### Randomization and blinding

Within each study region, participants will be assigned to either the intervention or the usual care group following the collection of baseline data, using stratified permuted block randomization administered by a centralized web-based service (RedCap) to allocate clients at each site to the two groups in accordance with the sequence and using a 1:1 ratio. All study participants will be blinded to their group allocation (usual care or CAST intervention). Research assistants completing further assessments with participants following recruitment will remain blind to group assignments for the duration of data collection. Upon completion of the study at 12-months, participants will receive a mailed debriefing letter describing the two groups and their group allocation.

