##### Cost of use of health and social services

The study will link participants to Institute for Clinical Evaluative Sciences (IC/ES) administrative databases to identify the use of emergency room visits, hospital admissions, use of family physicians, physician specialists, and home care services, and transfers to long-term care. In addition, the Health and Social Services Utilization Inventory (HSSUI) [63] will be used to measure the utilization of health and social services as reported by study participants and caregivers over the duration of the study. The HSSUI consists of questions about the respondent’s use of six categories of direct healthcare services: a) primary care; b) emergency department and specialists; c) hospital days; d) seven types of other health and social professionals; e) prescribed medications; and f) lab services. The data from the HSSUI will be used in combination with the IC/ES administrative data as a back-up in case we are unable to obtain IC/ES data at all three timepoints.

The six-month cost data will be derived from the product of “quantity” data reported on the HSSUI and 2015–2016 “price” data obtained by our team for the HSSUI [64]. The costs of use of health and social services will include the costs associated with delivery of the nurse-led intervention. This will form the basis of the cost-analysis, from a societal perspective that will compare changes in the costs of use of health and social services between participants in the intervention and control groups from baseline to 6- months, and from 6-months to 12-months post intervention. A complete copy of the HSSUI questionnaire is included as supplementary data (see Additional files 1 and 2). Table 1 provides an overview of the effectiveness evaluation, including the outcome, measures, group, and tiepoint for data collection.

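### The between-arm risk difference for ED visits and readmissions names no baseline covariate, although acute care use is collected before randomisation: a small, cheap gain in precision is left out

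*Protocol article*

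**What the plan says.** In the protocol article, the section Analysis: effectiveness evaluation gives the between-arm acute-care effect as a "Risk difference (intervention risk – control risk) and accompanying 95% confidence limits", computed at 6 months for ED visits and readmissions. No covariate is named. The utilization row of Table 1 adds "Hazard Ratio (95% CI) & Risk Difference (95% CI) for 30, 90 &180-day ED visits and hospital admissions", also without a covariate.

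For the continuous outcomes, the same section does name one. The ANCOVA takes "the group indicator as the independent variable and the baseline outcome value as the covariate".

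Pre-randomisation data on acute care use are planned. The utilization row of Table 1 lists T1 as a time point. The section on cost of service use says participants will be linked to administrative databases "to identify the use of emergency room visits, hospital admissions" and other services, with a self-report inventory as back-up "in case we are unable to obtain IC/ES data at all three timepoints". Allocation comes "following the collection of baseline data, using stratified permuted block randomization".

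The acute-care plan uses the T1 data in two places:

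- Z tests and McNemar tests of change in acute care episodes inside each arm, between T1 and T2 (and again between T2 and T3).
- A non-parametric test (Mann-Whitney U in Table 1) that compares the two arms on change in service use and costs.

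**The concern.** Earlier ED visits and admissions are a natural predictor of later ones. Where a baseline variable predicts the outcome, adjusting a randomised comparison for it narrows the interval and removes the part of the estimate that comes from chance imbalance in that variable. The article does this for the scale scores but, as written, not for the risk difference. That risk difference is the most readily interpreted randomised contrast for acute care.

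Reduced use of expensive services such as hospitalization is the second half of the stated hypothesis (Research questions), while the sample size was derived only for the mental component score of the VR-12. The acute-care intervals will therefore be wide, and precision available from data already planned has some value. The primary outcome is not affected.

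**Working it through.** **The plan's own figure.** Inputs from Sample size: difference 6.5, SD 15.0, power 80%, alpha 0.05 (taken as two-sided), attrition 20%.

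- Per arm: 2 × (1.96 + 0.84)² × 15² / 6.5², which rounds up to 84, or 168 in total. 168 / 0.80 = 210.
- With the t distribution: 85 per arm. 85 / 0.80 rounds up to 107, or 214 in total.

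Both are within 3% of the stated 216, so 216 (108 per arm at 1:1) is used below. The article gives no event risk, power or precision for the acute-care outcomes. The risks and the strength of the covariate below are therefore assumptions.

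**Unadjusted interval.** Assumed risks 40% and 30%, 108 per arm:

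- SE = √(0.4 × 0.6/108 + 0.3 × 0.7/108) = √(0.45/108) = 0.0645, or 6.5 points.
- 95% half-width = 1.96 × 0.0645 = 0.1265, or about 12.7 points.

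**Adjusted interval.** If the covariate explains a share R² of the outcome variance, the variance is multiplied by about (1 − R²). The equivalent gain in sample size is 216/(1 − R²) − 216. The assumed range of R², 1.5% to 10%, corresponds to odds ratios of about 1.2 to 1.8 per prior event when prior counts are over-dispersed.

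| Assumed R² | Half-width (points) | Equivalent extra participants |
|---|---|---|
| 0 | 12.7 | 0 |
| 1.5% | 12.65 × √0.985 = 12.6 | 216/0.985 − 216 = 3 |
| 10% | 12.65 × √0.90 = 12.0 | 216/0.90 − 216 = 24 |

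The upper R² is rounded; the simulated value was 9.5%, which gives 23 participants.

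**Second calculation, by correlation.** With a common risk of 40% and 108 per arm, the unadjusted half-width is 1.96 × √(2 × 0.24/108) = 13.1 points. At correlations of 0.1, 0.2, 0.3 and 0.4 between prior use and outcome, it becomes 13.0, 12.8, 12.5 and 12.0. The gain is equivalent to about 1%, 4%, 10% and 19% of the sample. Power for 40% against 25% is 65.5% unadjusted and 65.9%, 67.3%, 69.6% and 73.1% adjusted.

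**Simulation check.** This used 20,000 replicates with 108 per arm, a true difference of −10 points and linear adjustment for a yes/no prior-use covariate. Both estimators averaged about −0.10, so neither was biased. The ratio of unadjusted to adjusted variance was 1.01, 1.04, 1.11 and 1.22 at correlations of about 0.10, 0.20, 0.31 and 0.41.

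When 95% of participants had the prior event, the ratio was 1.00, even with control risks as far apart as 40% and 20%. That case matters here because every participant has just left hospital, so a yes/no prior admission that counts the index stay is close to constant.

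**The case against.** Several points can be made against this, and most of them stand in part.

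- **The article never calls the risk difference crude.** This is true. The bracketed formula gives the direction of subtraction, and a standardised risk difference is also one risk minus another. Table 1 names no covariate for its ANCOVA rows either, and those models are adjusted. An analysis plan that is not shown may add covariates. So no one can say that adjustment is ruled out. But the text of the section names the covariate for the scale outcomes and none for the risk difference, so the natural reading is unadjusted.
- **Baseline use is not ignored between the arms.** A reader might infer that T1 use plays no part in any randomised comparison. That is wrong: the non-parametric test of change in service use and costs compares the arms. It yields a test of change, however, and does not sharpen the risk difference.
- **The unadjusted estimate is sound.** A reader might infer bias or an invalid interval. Randomisation gives an unbiased estimate, and the interval already allows for chance imbalance on average.
- **The hazard ratio in Table 1.** A reader might extend the precision argument to it. That does not follow: the hazard ratio is non-collapsible, so a prognostic covariate changes the quantity being estimated and does not generally narrow its interval.
- **The covariate is not quite ready to use.** No lookback window is stated. The self-report inventory lists hospital days, not admissions, and groups ED visits with specialists. The article itself allows that linked data may not be obtained at every time point. This stands, and the fix has to deal with it.

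**Conclusion.** The point holds as a minor suggestion about a secondary outcome. As written, the risk difference for ED visits and readmissions leaves out a pre-randomisation variable that the trial plans to collect and that is likely to be prognostic. Nothing in the plan is invalid.

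Under the assumed risks and R² of 1.5% to 10%, the half-width falls by about 0.1 to 0.7 points, worth about 3 to 24 of 216 participants. The size cannot be derived from the article. It would be larger if prior use were more strongly prognostic, and close to zero with a yes/no prior admission that includes the index stay. The case for the change is that it costs very little, not that the present analysis would mislead.

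**What to change.** In Analysis: effectiveness evaluation and in the utilization row of Table 1:

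- Pre-specify the between-arm risk difference as standardised from a logistic model with arm and the T1 count of ED visits and admissions, with 95% limits.
- Define that count once: index stay excluded, one stated lookback window, and the same data source in both arms. State which source applies if linked data are not available for T1.
- Report the crude risks by arm and the crude difference with its interval beside the adjusted result.
- Leave the hazard ratio as it is. If an adjusted one is added, describe it as a different, conditional estimand and claim no gain in precision for it.

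The cost is a few lines of wording and code. No new data collection is needed if the linked data are obtained for T1. If only the self-report inventory is available, first confirm that the count can be formed from its items.
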